### Data Analysis

Descriptive statistics will be applied to the characteristics of the survey population. Categorical variables will be reported as percentages and compared using the chi-square test (and the Fisher exact test for small numbers). Continuous variables will be expressed as mean (SD) or median (IQR) values, and compared using Student and Wilcoxon signed ranked tests in accordance with the variable distribution. A simple logistic regression analysis will be applied to select variables associated with the outcome, and all variables with a *P* value of *<*.10 will be entered into a multiple logistic regression model for each outcome. Statistical analysis will be performed using STATA (version 11.2; StataCorp), and statistical significance will be defined as a *P* value of ≤.05.

Survival analysis will be used to analyze cumulative retention in care for 12 months after the beginning of the intervention. Differences between survival curves will be assessed at month 12 using the Kaplan-Meier estimate (log-rank test).

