### Key Outcomes for Each Phase of the Study

The key outcomes of phase 1 will be the analysis of the verbatim responses of MWSWs and institutional actors about the determinants of PrEP use, those of phase 2 will be the estimated number of MWSWs in Marseille, those of phase 3 will be the number of MWSWs included in the longitudinal study and quantitative analysis of the questionnaire data, and those of phase 4 will be the number of consultations for sexual health, access to rights, and PrEP uptake among MWSWs before and after the interventional phase.

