### Phase 3: Representative Cohort Formation Through RDS and Follow-up

The inclusion criteria are being a cis- or transgender woman older than 18 years, self-reporting as having changed their sex for money or other resources during the past 12 months, having been born outside of France, living or working in the city of Marseille, and agreeing to participate in the study.

Numerous studies have demonstrated the effectiveness of RDS to engage adults in HIV research, particularly in stigmatized communities [29,30]. Initial RDS participants (ie, “seeds”) will be recruited for the study to achieve good representativeness in terms of the type of community or nationality, sex work (eg, indoor, outdoor, via the internet), place of residence in Marseille, and gender (cis- or transgender women). The prior qualitative study will make it possible to clearly define the characteristics of representativeness. Approximately 150 participants are expected to be enrolled in the cohort. At the beginning, participants will be offered 3 coupons. Participants who meet the eligibility criteria will be provided with a food coupon worth €10 (US $10.86) for completing each part of inclusion and follow-up (at months 3, 6, and 12), and another food coupon worth €10 (US $10.86) for each eligible and participating peer recruited. In addition, FASSETS study participants will be given public transport tickets, free condoms, and lubricating gel.

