### Data Collection

Upon enrollment and at months 3, 6, and 12, participants will be asked to complete a structured survey administered by a CHW. The survey will include questions regarding network size for RDS weighting. These will include questions about the token given at the time of data capture. Individual data including sociodemographic characteristics; sexual practices; knowledge and behavior; HIV testing history; medical history; PrEP knowledge, adherence, and compliance; contraception; drug and alcohol use; mental health (including Perceived Stress Scale-10 scores); quality of life; literacy; social support; being subjected to racism; stigmatization or violence during the past 12 months; and mobility will be collected. Other more structural determinants will be collected as follows: residence permits, health insurance, housing conditions, and food security (Table 1). Indeed, such structural determinants are previously described to have a significant impact on health care access among sex workers [42]. The semistructured questionnaire will explore the barriers and levers to accessing PrEP among MWSWs. The instrument or interview guide will attempt to understand how PrEP fits into women’s needs, care pathways, and mobility. Representation of MWSWs’ PrEP uptake among caregivers and which mechanisms are (or are not) implemented by social institutions to facilitate access to prevention and care for MWSWs (Table 1).

Type, objective, and number of actions of mediation in terms of prevention, support, or access to health care or social services will be self-reported by CHWs.

CHWs will use encrypted and secure survey software to report the MWSWs’ responses to the questionnaires and to monitor their actions of mediation. All electronic questionnaires will be forwarded to a database that is managed and hosted by SESSTIM (Inserm laboratory in Marseille). Each staff member will have a secure individual account.

Databases of all NGOs and institutional screening and PrEP centers of Marseille will be retrospectively analyzed to describe the HIV status and to assess PrEP characteristics among migrants and women in Marseille.

**Table 1 table1:** Data collection tools and timing.

Method	Timing	Population	Data collected

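### For binary before/after outcomes in the same women, the Data Analysis section names only independent-sample tests and a logistic model with no within-person term

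*Protocol article*

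**What the plan says.** The section on key outcomes sets the phase 4 outcomes as the "number of consultations for sexual health, access to rights, and PrEP uptake among MWSWs before and after the interventional phase". The Data Collection section makes clear that the same women are measured repeatedly: "Upon enrollment and at months 3, 6, and 12, participants will be asked to complete a structured survey administered by a CHW". On size, the phase 3 section says "Approximately 150 participants are expected to be enrolled in the cohort". The Limitations section explains that a control group was not possible. It rests the evaluation on pre/post comparisons and on comparisons of participants with nonparticipants.

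The Data Analysis section names these methods:

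- Categorical variables: "Categorical variables will be reported as percentages and compared using the chi-square test (and the Fisher exact test for small numbers".
- Continuous variables: "compared using Student and Wilcoxon signed ranked tests in accordance with the variable distribution".
- Regression: univariable logistic models first, after which "all variables with a *P* value of *<*.10 will be entered into a multiple logistic regression model for each outcome".
- Retention in care: Kaplan-Meier and log-rank.

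It does not say which test serves which comparison.

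**The concern.** Chi-square and Fisher tests compare two independent groups. A month 0 proportion and a month 12 proportion from the same women are not independent. Residence permits, insurance, housing and knowledge tend to persist within a person, so positive correlation is the natural expectation. Ignoring it inflates the standard error of the change. Real gains in rights, insurance, testing or knowledge could then be reported as non-significant, in a study where within-woman change is central evidence because there is no control arm. An ordinary logistic model that pools rounds without a participant term makes the same independence assumption.

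The continuous branch has the reverse fault. The signed-rank test is valid only for paired data, so the list offers no rank test for two separate groups, and the Student test is not identified as paired or unpaired.

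**Working it through.** The article gives no effect size, power or sample-size calculation, so there is no figure of its own to reproduce.

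**Inputs.** From the protocol article: n of about 150, significance at 0.05 (two-sided assumed), the same women before and after. Assumed, because the article gives none of them: proportion before p0 = 0.30, after p1 = 0.40, within-woman correlation (phi) 0 to 0.7, no loss to follow-up, and women independent of one another.

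**Cell probabilities.** P(yes both times) = p0·p1 + phi·√[p0(1−p0)·p1(1−p1)], where √(0.3×0.7×0.4×0.6) = 0.2245. At phi = 0.3 this is 0.12 + 0.0673 = 0.1873. The discordant probabilities are then 0.30 − 0.1873 = 0.1127 (yes before only) and 0.40 − 0.1873 = 0.2127 (yes after only), with sum 0.3253.

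**Standard error of the change.**

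- Treated as independent: √[(0.21 + 0.24)/150] = 0.055 at every phi.
- Paired: √[(sum of discordants − 0.10²)/150]. At phi = 0.3: √[(0.3253 − 0.01)/150] = 0.046.

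**Tests at expected counts (45/150 against 60/150).**

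- Chi-square: z = 0.10/√(2×0.35×0.65/150) = 0.10/0.0551 = 1.82, p = 0.069 whatever phi is.
- McNemar: 150×0.10²/(sum of discordants). At phi = 0.3: 1.5/0.3253 = 4.61, p = 0.032.

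**Power and true size** (simulated correlated pairs, 40,000 runs; size is for 30% at both times):

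| phi | SE paired | McNemar p | Power chi-square | Power McNemar | Power exact McNemar | True size of 5% chi-square |
|---|---|---|---|---|---|---|
| 0 | 0.055 | 0.071 | 44% | 44% | – | 5.1% |
| 0.3 | 0.046 | 0.032 | 43% | 58% | 53% | 1.9% |
| 0.5 | 0.039 | 0.012 | 41% | 73% | 67% | 0.6% |
| 0.7 | 0.030 | 0.001 | 39% | 93% | 90% | under 0.1% |

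The size agrees with 2[1 − Φ(1.96/√(1 − phi))]. At phi = 0.3, 1.96/0.837 = 2.34, which gives 1.9%.

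**With 30% loss (assumed; 150×0.7 = 105 women).** At phi 0.3, 0.5 and 0.7, power is 30%, 27% and 21% for chi-square, against 44%, 59% and 81% for McNemar.

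**PrEP uptake.** The Introduction reports 7 migrant women sex workers among 2197 people consulting for PrEP. That is not a prevalence in the cohort, but it suggests a baseline near zero. With 0 users before and 6 of 150 after, Fisher gives p = 0.030 and exact McNemar gives 2×(1/2)⁶ = 0.031. With 5 after, the values are 0.060 and 0.063. The two exact tests cross 0.05 at the same count. For an assumed rise from 0.3% to 10%, power is 99.5% or more with chi-square and with asymptotic McNemar.

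**The case against.** The strongest reply is that the section never assigns chi-square or Fisher to the before/after contrast. The sentence follows one about describing the survey population, and these tests suit baseline subgroups and participants versus nonparticipants. That is true and limits the point. It does not remove it, because no reading makes the named tests a coherent set. If the section covers before/after change, chi-square and Fisher are wrong for binary outcomes. If it covers between-group comparisons, the signed-rank test is wrong. If it covers both, it names no valid test for a binary before/after outcome and none for a skewed between-group comparison.

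A second reply is that a condensed article may leave detail to an analysis plan. Here, however, a type of test is named, and it does not suit the stated contrast.

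A third reply is that the illustration is assumed throughout. This stands: at zero correlation nothing is lost, exact McNemar gains less than the asymptotic version, and dependence between women recruited through one another's networks is not modelled.

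Several stronger readings are tempting but not supported:

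- That all before/after changes are tested as if independent. The signed-rank test is paired, and the Student test may be.
- That most phase 4 outcomes lose power. Of the three named, consultations are a count and fall in the continuous branch, and PrEP uptake is little affected if baseline use is near zero. Retention is analysed by survival methods.
- That months 3 and 6 are left out of the effect estimate. The article defines no such estimate and excludes no round.
- That the named tests lose women who leave before month 12. An unpaired chi-square keeps their baseline data; McNemar and the paired t test are the ones that need both rounds.

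**Conclusion.** The point holds for binary before/after outcomes in the same women. For these the article names only independent-sample tests and a logistic model without a within-person term. In the illustration the power lost, relative to asymptotic McNemar, is nil at zero correlation and about 15, 32 and 54 percentage points at 0.3, 0.5 and 0.7. This rests on assumed rates of 30% and 40%, 150 complete pairs and independent women. It would apply to access to rights if that is coded yes/no, and to items such as insurance, PrEP knowledge and HIV testing.

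Under positive correlation the error is conservative: it can hide a gain but does not raise the false-positive rate. It leaves the conclusion on PrEP uptake almost unchanged if baseline use is near zero. The continuous branch needs clarifying rather than replacing. This should be corrected before analysis, but it does not undermine the study's main PrEP outcome.

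**What to change.** In the Data Analysis section, match each test to its contrast:

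- Binary, before/after in the same women: McNemar (exact when discordant pairs are few), or a logistic GEE or mixed model with participant as cluster and visit (months 0, 3, 6, 12) as a factor. Report the month 12 versus month 0 change with its 95% confidence interval. The model can use every available round, whereas McNemar uses only women seen at both times.
- Continuous, before/after: paired t or signed-rank, with the word paired stated.
- Between groups, such as participants versus nonparticipants or baseline subgroups: chi-square or Fisher, unpaired t, and rank-sum in place of signed-rank.

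The cost is a few sentences. The repeated questionnaires are already planned, so no new data are needed.

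### Logistic regression is the only adjusted model and is prescribed for every outcome, but the number of sexual health consultations is a count and needs a count model

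*Protocol article*

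**What the plan says.** The Key Outcomes section of the protocol article lists, for phase 4, "the number of consultations for sexual health, access to rights, and PrEP uptake among MWSWs before and after the interventional phase". The first of these is a count. PrEP uptake is yes/no for each woman, and access to rights may be recorded that way.

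The Data Analysis section describes one regression strategy. "A simple logistic regression analysis will be applied to select variables associated with the outcome", and those with P below .10 are then "entered into a multiple logistic regression model for each outcome". No count or linear model is named.

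Two other analyses appear in the same section. Continuous variables are to be "compared using Student and Wilcoxon signed ranked tests in accordance with the variable distribution". For retention, "Survival analysis will be used to analyze cumulative retention in care for 12 months after the beginning of the intervention", with a log-rank test. Neither adjusts for covariates.

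On size, the Phase 3 section says: "Approximately 150 participants are expected to be enrolled in the cohort".

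**The concern.** Binary logistic regression cannot take a number of consultations as its response. If the rule is applied to every outcome, the count must first be split, either any versus none or above versus below a threshold. A woman with one consultation and a woman with six then look the same under any versus none. If the threshold is chosen after the data are seen, it can also change which determinants reach significance.

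The adjusted analysis has a purpose here. The first study objective is to analyse determinants of access to sexual health care, and many individual and structural determinants are collected. With about 150 women, there is little information to spare for estimating such associations.

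**Working it through.** **No figure to reproduce.** The article states no consultation rate, dispersion, effect size or power, and 150 is given as an expected number without a derivation. What follows is an illustration under assumptions.

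**Inputs**
- From the article: n = 150 and a significance level of 0.05.
- Assumed: a two-sided test; a binary determinant split 75/75; consultations Poisson or negative binomial, with reference-group mean μ₀ from 0.5 to 4 and dispersion a from 0 to 2.

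**Step 1, count model.** With rate ratio RR and μ₁ = μ₀ × RR,

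var(log RR) = (1/μ₀ + a)/75 + (1/μ₁ + a)/75, and power = Φ(log RR / SE − 1.96).

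In each setting RR is chosen so that this power is 80%.

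**Step 2, yes/no model.** The same distributions are cut at k or more consultations. Power for the two resulting proportions is

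Φ[(|p₁ − p₂| − 1.96 × SE₀) / SE₁],

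with SE₀ from the pooled proportion and SE₁ from the separate ones. This is a large-sample stand-in for the logistic test.

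**Worked case: μ₀ = 2, a = 0.5**
- 80% power needs RR = 1.548. The SE is 0.156, log RR / SE = 2.80, and Φ(2.80 − 1.96) = 0.80.
- Any versus none: 0.750 against 0.846, power 0.31.
- Two or more: 0.500 against 0.659, power 0.50.
- Three or more: 0.313 against 0.488, power 0.59.
- Four or more (the best cut): 0.188 against 0.350, power 0.61.
- Five or more: 0.109 against 0.245, power 0.59.

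**All settings (count model at 0.80 throughout)**

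| Reference mean | Any vs none | Best cut |
|---|---|---|
| 0.5 | 0.52–0.67 | 0.62–0.67 |
| 1 | 0.41–0.51 | 0.60–0.65 |
| 2 | 0.28–0.31 | 0.60–0.63 |
| 3 | 0.15–0.25 | 0.60–0.62 |
| 4 | 0.09–0.22 | 0.60–0.62 |

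The best cut loses 80 − 67 = 13 to 80 − 60 = 20 points. Any versus none loses 13 to 80 − 9 = 71 points, and more as consultations become more frequent. The best cut moves from one or more to twelve or more across the settings, so it cannot be known in advance.

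**Step 3, the before-after comparison.** Paired gamma-Poisson counts were simulated with 1,500 runs per setting, means before the intervention of 0.3 to 3, rate ratios of 1.2 to 1.6 and dispersion of 0.5 to 2. At n = 150 the signed-rank test on the counts had power 0.66 to 0.80. An exact McNemar test on any versus none had 0.09 to 0.54 in the same settings. The planned signed-rank test uses the count itself and avoids that loss.

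**The case against.** The strongest reply is that the article never says consultations will be dichotomised. The outcome is defined as a before-after comparison, and the planned Student and signed-rank tests handle that on the full count. This stands: a reader might infer that the consultation outcome as a whole must be reduced to yes/no, but only the adjusted analysis is exposed.

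Second, logistic regression fits what the study mainly evaluates. The Introduction judges the intervention by the number of women taking PrEP at the end of follow-up, and retention has its own survival analysis. This also stands, so the mismatch concerns one of three key outcomes.

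Third, the phrase could be shorthand for each binary outcome, and an article may leave model families to a fuller document. That is plausible, but the article goes beyond silence: it names a model and assigns it to every outcome. The finding rests on that assignment, not on missing detail.

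Three stronger readings lack support:
- **A large loss of power is established.** It is not, because every rate and effect above is assumed and the loss depends on the cut.
- **Women who leave early are excluded from the adjusted model.** The article does not say so.
- **The stress and quality-of-life scores are also mis-modelled.** The Data Collection section lists "mental health (including Perceived Stress Scale-10 scores); quality of life; literacy; social support" as data to be collected, and nowhere are these made outcomes.

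**Conclusion.** The point holds in a limited form. As worded, the adjusted-model rule does not fit the number of sexual health consultations and, taken literally, forces a cut in that analysis. The unadjusted before-after test and the logistic model for PrEP uptake are sound in this respect.

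The illustrated cost is a fall from 80% power to about 60% to 67% at the best cut, and to below 60% in 18 of the 20 any-versus-none settings. These figures assume 150 women with data, an even split on a between-woman determinant and the stated count distributions. They show that the choice of model can matter at this sample size; they do not estimate this study's power.

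**What to change.** In Data Analysis, restrict logistic regression to binary outcomes: PrEP uptake, and access to rights if recorded as yes/no.

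For the number of consultations per woman, name a negative-binomial model, or Poisson with robust errors, with log observed time as offset and rate ratios reported. Where before and after are modelled together, add a period term and allow for within-woman correlation; an offset alone does not represent that comparison.

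The offset keeps women with partial follow-up in the model. It does not remove bias if those who leave early use care at a different rate.

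The cost is mainly wording, and rate ratios replace odds ratios for this outcome. One condition needs checking: the Key Outcomes section implies a count per woman, but neither the survey content in Data Collection nor Table 1 lists one. It must be obtainable from the questionnaires or the centre databases.

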### Ethics Approval and Consent to Participate

The protocol received approval from French Ethics Committee in October 2021 (2021—A01746-35). Prior informed consent of the participants will be collected by a member of the research team before data collection. All the participants are free to withdraw from the study at any moment without incurring any penalties or consequences with regard to future care or services they might rightfully expect.

The study protocol has also been reviewed and approved by an independent peer review for funding by Sidaction.

Planned dissemination of study findings includes manuscript publication, conference presentations, and community dissemination (eg, community meetings and social network).

## Results

Recruitment commenced on March 1, 2022. We estimate that the follow-up period will end on September 30, 2023.

## Discussion

### Anticipated Findings

Community empowerment interventions that aim to reduce the risk of HIV acquisition using PrEP among MWSWs are scarce worldwide. To our knowledge, this is the first intervention of its kind in Europe. Innovative and community-based approaches to bring MWSWs closer to health and social services are required. The findings from the FASSETS study will prove useful for tailoring PrEP use, proposing PrEP use to MWSWs and ensuring its adherence among them, and developing a sustainable community-based intervention.

One of the main challenges of this study is to take into account all the barriers to access to care in this vulnerable population and possibly the low prioritization of PrEP in light of their vital needs. Indeed, MWSWs have to deal with many structural factors such as the criminalization of their work, stigmatization, racism, or their precariousness [17,42]. This project, through a holistic approach based on the needs of the participants, aims to work on the issue of empowerment in a transversal approach. CHWs will be trained in sexual health prevention and will help the participants better access their rights and basic needs, especially those of housing, civic rights (eg, resident permit and social insurance), and access to food. Regarding the fight against stigmatization and racism, this study aims to set up a collective empowerment program with the help of CHWs for better consideration of their difficulties. Partner NGOs such as The Truth and AIDES will participate in advocacy in accordance with the difficulties encountered by the participants. Moreover, CHWs’ actions have been previously described as having a social transformation impact [43].

The FASSETS intervention team has the capacity to provide cohort follow-up and individual and collective empowerment actions through partnerships with local organizations interested in connecting with the population of MWSWs. This team includes CHWs from multiple countries and cultures. FASSETS participants will have greater access to services, and health organizations may be able to reach a wider segment of the population to propose the use of PrEP.

FASSETS is a comprehensive, interdisciplinary, participatory study that combines clinical, epidemiological, and social sciences. Research questions are not limited to the participants and they take the health care network and implementing staff into consideration, notably with health mediation descriptions.

